**Fig. 2 Fig2:**
[figure not shown]
The study sampling stages

$$n= \frac{{2\left(Z1-\frac{\alpha }{2}+ Z1-\beta \right)}^{2}}{{\left(\frac{\Delta }{S}\right)}^{2}}$$

The schools selected for the intervention and control groups will be far apart in order to prevent contamination bias. The effects of confounding variables such as economic status and social class will be controlled in the clusters in the data analysis with the covariance test. All samples, education office, school managers, and user panel managers will be blinded.

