#### The third stage

The next stage of the sampling method is cluster random. From 337 government schools and 93 non-government schools, based on the list of urban schools received from the Department of Education, two boys’ schools and two girls’ schools are randomly selected. Then, one boy’s school and one girl’s school will be randomly assigned as the intervention group and one boy’s school and one girl’s school will be in the control group, and the sampling of students of different grades of the selected schools will be simple cluster or random. Sampling of students from different grades from selected schools will be simple in cluster or random. The sample size was calculated according to the formula of 43 people in each group. Taking into account 15% attrition, the sample size was determined to be 50 people in each group. The study will be conducted on 100 students of Amol City. Of these, 50 people will be assigned to the intervention group and 50 people will be assigned to the control group. From each school, 25 samples were selected (Fig. 2).

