#### Stage III

The third stage is an interventional method of experimental study. This research will be conducted through a pre-test-post-test design with a control group. All the students studying in schools constitute the research community. The researcher first introduces the adolescents to the full explanation of the research and its goals. Then informed written consent will be obtained from the volunteers. None of the participants will be subject to any other research intervention. Schools will be randomly assigned to one of the two intervention (group 1) and control (group 2) groups. The full content of the program will be visible only to the participants in the intervention group. Participants in the control group will be able to download the app after the end of the intervention to use the educational benefits of the app. A self-care application can be used online and offline designed for smartphones running the Android operating system. To run this test, eligible students are asked to install the self-care app on their smartphone and see the necessary instructions on how to work with the program in the form of a short guide on the main page of the application. Initially, the participants are asked to complete the self-care questionnaire in the form of a pre-test. Then, the educational content designed for the application is provided for individuals based on national and international guidelines and protocols of (WHO, CDC, FDA, ADF, Ministry of Health and Medicine, Health Education and Health Promotion Office). This program will be available to people for 3 months and after installing the application on their smartphone and entering the information requested from the users, educational content and reminder messages will be sent according to their conditions. In the reminders section, the user registers his health behavior based on the day, time, and number of times he wants, and a reminder is sent to him. But if the user’s self-care status after answering the self-care questions in each of the 5 dimensions of self-care is assessed as weak or average, motivational health messages are sent to the user daily in the form of notifications, so that the user is encouraged to perform self-care behaviors. The use of the application by the participants is reviewed in the management panel and health messages and incentives are provided for the use of this program. To provide support, the researcher’s phone number is given to the subjects to make a call in case of problems. Three months after the intervention, when no new content is sent to the student, the participants in both groups are requested to complete the self-care questionnaire in the form of a post-test. After the end of the data collection process, the individuals in the control group can install a mobile Application and the necessary training will be given to them after the end of the study. In the present study, content, information, and experiences reach the end users or audience with the specific purpose of self-care through mobile applications in the form of text, audio, or other art forms. Users find and use health-related self-care information through content. The graphic design of the application is based on the opinion of the research team professional designers and application development experts. The production of the content is based on the points extracted from the interviews, national and international guidelines, and protocols of (WHO, CDC, FDA, Ministry of Health and Medicine, Health Education and Health Promotion Office), for example, Australian dietary guidelines, Canberra: NHMRC [20], WHO guidelines on physical activity and sedentary behavior for children and adolescents aged 5–17 years: summary of the evidence [21], and physical activity guidelines [22].

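### The blinding statement contradicts the open design for pupils and panel managers, and the protocol gives two conflicting orders for allocation, sampling, consent and pre-test.

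*Protocol article*

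**What the plan says.** In the protocol article, the paragraph after Fig. 2 (Sampling method, third stage) says: "All samples, education office, school managers, and user panel managers will be blinded".

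The text of the same section just before Fig. 2 describes selecting two boys' and two girls' schools, after which "one boy’s school and one girl’s school will be randomly assigned as the intervention group". The remaining two schools form the control arm, and pupil sampling comes next: "in the control group, and the sampling of students of different grades of the selected schools will be simple cluster or random".

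Study process, Stage III, gives its own sequence:

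- "The researcher first introduces the adolescents to the full explanation of the research and its goals"
- Written consent is then taken from volunteers.
- The assignment of schools to the two arms is stated after that.
- Full app content is reserved for the intervention arm; controls may download the app once the intervention is over.
- "eligible students are asked to install the self-care app on their smartphone"
- "Initially, the participants are asked to complete the self-care questionnaire in the form of a pre-test"
- Educational content, reminders and motivational messages follow for 3 months.
- "The use of the application by the participants is reviewed in the management panel"; messages and incentives are provided as well.

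Data collection methods (third stage) adds that the questionnaire is loaded on the app and that both groups complete it themselves as the post-test.

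**The concern.** There are two separate problems.

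First, the article claims blinding for people whom the described procedures inform of the arm. The pupil is both participant and outcome assessor, because the only effectiveness measure is a questionnaire that the pupil fills in. A reader who accepts the claim would take performance and detection bias to be controlled when they are not.

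Second, when whole schools are allocated, a main safeguard is to enrol pupils and measure baseline before the allocation is revealed. Otherwise pupils in an app school may volunteer at a different rate, or answer the baseline differently, from pupils in a waiting school. With two schools per arm, randomisation alone gives little protection against imbalance. The article gives two sequences that do not agree, so it cannot be read as securing this safeguard.

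**Working it through.** **Blinding: the claim set against the described procedures.**

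| Group said to be blinded | What Stage III describes | Can the claim stand? |
|---|---|---|
| Pupils | Told the goals in full; then have or lack the full content, reminders and messages for 3 months | No |
| User panel managers | App use is reviewed in the panel they manage; only one arm has the full content | No, on the natural reading |
| School managers | No role described that reveals the arm, though their pupils either use the app content or wait for it | Implausible, not excluded |
| Education office | No role in delivery described | Not contradicted |

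No section describes a sham app or attention control that could keep a pupil who knows the aims from recognising the arm.

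**Order of steps: the two accounts.**

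- Sampling method: select schools → allocate schools → sample pupils. Consent and pre-test are not placed.
- Stage III, in order of writing: explain → consent → allocate schools → install app → pre-test → release content.

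Consent requires a sampled pupil. If sampling follows allocation, as in the first account, consent does too. The second account writes consent before allocation. Both cannot be right. In the second account the pre-test follows allocation, though it precedes the educational content. Neither account says whether the allocation is concealed from pupils or recruiters at any step.

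**Size: what can and cannot be computed.**

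The plan's own figures come first. Inflating 43 per group by 15% gives 43 × 1.15 = 49.45, rounded up to the stated 50 (43/0.85 = 50.6 would give 51). Four schools × 25 = 100 agrees with the total. The 43 itself cannot be reproduced, because alpha, power, Δ and S are not stated. It can only be solved backwards from the printed formula, assuming two-sided alpha 0.05:

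- Δ/S = √[2(z₁₋α/₂ + z₁₋β)²/43]
- 80% power: √[2(1.960 + 0.842)²/43] ≈ 0.60
- 90% power: √[2(1.960 + 1.282)²/43] ≈ 0.70

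Purely as an illustration, assume no true effect and a bias of b SD between arms, with 43 independent pupils per arm. The standard error is √(2/43) ≈ 0.216 SD, and the rejection rate is 1 − Φ(1.96 − b/0.216) + Φ(−1.96 − b/0.216).

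| Assumed b (SD) | Share of 0.60 | Share of 0.70 | Rejection rate |
|---|---|---|---|
| 0.1 | 17% | 14% | 7.5% |
| 0.2 | 33% | 29% | 15% |
| 0.3 | 50% | 43% | 29% |

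Nothing in the documents supports any particular b. The calculation ignores clustering, so even the 5% starting point is not what a design with two schools per arm delivers. It also does not separate recruitment and baseline bias from post-test self-report bias.

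**The case against.** The strongest defence concerns the order of steps. Stage III writes consent before allocation, which is the favourable sequence, and places the pre-test before any educational content. Installing the app before the pre-test may only be how the questionnaire is delivered, since Data collection methods says it is loaded on the app for both groups. If controls hold a restricted version, installation alone reveals nothing. The article leaves this unclear, because it also says that controls download the app only after the intervention. Random sampling within schools further limits who is approached, although it does not govern who agrees.

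This defence stands in part. A reader might infer from Sampling method that consent, volunteering and baseline answers all occur with the arm known. The documents do not support that: no section says the arm is announced by then, and Stage III points the other way for consent. What remains is a conflict between sections and no described concealment.

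A reader might also infer that none of the listed groups could be blinded. That goes too far for school managers and the education office, who are given no task that discloses the arm. For panel managers, the text says that use is reviewed in the panel without naming the reviewer, so the conclusion rests on the natural reading that those who manage the panel see what it shows.

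None of this rescues the claim for pupils. A restricted control version of the app would not blind someone who knows the goals and lacks the full content for 3 months.

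**Conclusion.** The blinding statement is wrong as written for pupils and, on the natural reading, for panel managers. This follows from the text alone and needs no numerical assumption. Since pupils rate their own outcome, the trial cannot be described as blinded.

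The recruitment point holds in a narrower form. Sampling method places pupil sampling after allocation, Stage III places the pre-test after allocation, and the two sections disagree about consent. Differential volunteering and arm-aware baseline answers are therefore possible but not established.

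No magnitude can be attached from the documents. It would be tempting to say that the false-positive rate rises to about 29%. That figure rests on an assumed bias, an unstated power for the comparison with the planned effect, and independent pupils. It also includes post-test self-report bias, which no reordering of recruitment can remove.

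**What to change.** 1. Replace the blinding sentence with a statement that pupils and panel managers are not blinded, and that the estimated effect is on self-reported self-care in unblinded pupils. Claim blinding of school managers or the education office only if the procedure that achieves it is described.
2. Reconcile Sampling method and Stage III to a single order: select the four schools; sample and consent pupils; complete the pre-test in all four schools; draw and reveal the school allocation; release the app content.
3. If Stage III enrolment has already taken place, report the order actually followed and whether the arm was known at consent and at pre-test. Trial status gives first recruitment as July 26, 2022, ahead of the protocol version of May 12, 2023, but does not say which stage this refers to, so reordering may no longer be possible.

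The cost is small. Item 1 is wording, item 2 rearranges steps already planned, and item 3 is reporting. The one practical downside is that the app content cannot start in any school until all four have finished the pre-test. Reordering protects recruitment and baseline only; the self-report limitation at post-test remains and has to be acknowledged.

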### Study process

#### Stage 1

In the first stage, in line with the principles of user-centered design, the design consists of four key steps:Assess the needs of end users through in-depth interviews with stakeholdersDesign functional modules and evidence-based content based on the end needs of usersDesign and development of M-Health system structure and user interface based on the role and characteristics of end usersImproving and upgrading the system through the evaluation of the final program

Step 1: This step examines the needs, preferences, and priorities of adolescents, parents, and health professionals about a mobile self-care app for adolescents. At this stage, individual interviews are conducted with parents and adolescents separately. Considering that the purpose of this study is to design a mobile application with the topic of self-care in adolescents, three subgroups of experts, parents, and adolescents can be used for the interview. While the guide questions will have slight differences in the three subgroups, they should cover two sections related to app features and self-care content. In general, the guide questions will be set according to the review of the texts and the expert opinions of the research team (Table 1). For example, in the content section, based on a review of the texts, 5 sections were considered for the physical dimension of self-care, which is discussed in the interviews. During the interviews probing questions can be used to collect more data.

**Table 1 Tab1:** Interview guide

Adolescents
✔ How do you define self-care?
✔ What measures do you take to take care of yourself? Why?
✔ Who do you think should help you take care of yourself?
✔ What do you think about having a website and smartphone app that can help you better manage your self-care?
✔ How do you want to track information and actions related to self-care in an app? what information?
✔ How do you want to perform better in the app to help you set self-care goals?
✔ If there is to be an app in the field of health with 5 sections (physical activity, nutrition, risky behaviors, and safety and events), what do you think about the educational content of these sections and how to present them?
Parents
✔ How do you define self-care?
✔ How long and how has your adolescent been active in the field of self-care?
✔ Do you think your adolescent wants to develop self-care practices? Why? Why not?
✔ What tools and resources do you feel your adolescent has to manage their own care independently?
✔ What do you think about having a website and smartphone app that can help your adolescent manage and develop better self-care?
✔ How regularly does your adolescent track their self-care activities? (for example, in paper or electronic form) Why not?
✔ About self-care management, what information do you or your adolescent want to feel comfortable with self-care?
✔ If there is to be an app in the field of health with 5 sections (physical activity, nutrition, risky behaviors and safety and accidents), what do you think about the educational content of these sections and how to present them?
Experts
✔ What do you say are the biggest challenges and obstacles for adolescents and families in self-care?
✔ Do you feel they have the tools and resources needed to manage self-care independently?
✔ What do you think about having a website and smartphone app that can help adolescents manage and develop better self-care?
✔ How do you see the main and practical themes of a suitable app for the care of adolescents?
✔ Are there other important features that we haven’t talked about that can help them become healthier?
✔ If there is to be an app in the field of health with 5 sections (physical activity, nutrition, risky behaviors, and safety and accidents), what do you think about the educational content of these sections and how to present them?

Step 2: Content quality is one of the most important aspects of reputable health programs. Interviews and discussions will be held on the main topics of the content and features of the program. To ensure the quality of health information provided in the program, a review of the texts is carried out. Information on the main themes of the self-care program will be obtained from national and international guidelines (WHO, CDC, FDA, ADF, Ministry of Health and Medicine, Health Education, and Health Promotion Office).

Step 3: After specifying the functions and modules, the system architecture is designed. To ensure a user-friendly interface, a smart mobile application will be designed by professional designers and application development experts with full consideration of user needs. The user interface should be designed in a friendly and efficient way, which is critical in improving the user experience in using and interacting with the app. This program has three main innovative features: privacy, program updates, and simple and automatic transfer of self-care programs related to user health status. This app will be designed for the popular Android operating system smartphones. This operating system (OS) has widely been used in mobile phones worldwide, in particular in those which are common in the Iranian market and we chose the Android OS to avoid limitations that could be experienced with other less common OS in our context of use.

Step 4: Evaluate the final program. In this step, the usability of mobile applications for adolescent self-care is evaluated from the perspective of students and health professionals. At this stage, 15 male and female students are randomly selected and 15 health professionals are selected by available sampling and are asked to install the final version of the self-care program on their mobile phones. After 2 weeks of using the program, participants are asked to answer the Mobile Health App Usability Questionnaire (MAUQ). The Mobile Health App Usability Questionnaire (MAUQ) has 3 subscales and 18 questions: the first part is related to ease of use (5 questions), the second part is user interface and satisfaction (7 questions) and the third part is about usefulness (6 questions) [19].

#### Stage II

In the second stage, with an organized review of available sources and articles based on the concept of self-care, the items of the “Questionnaire for Measuring Self-Care Performance in Adolescents” will be extracted. Next, the validity (face, content, and construct) and reliability of the designed questionnaire will be determined.

#### Stage III

The third stage is an interventional method of experimental study. This research will be conducted through a pre-test-post-test design with a control group. All the students studying in schools constitute the research community. The researcher first introduces the adolescents to the full explanation of the research and its goals. Then informed written consent will be obtained from the volunteers. None of the participants will be subject to any other research intervention. Schools will be randomly assigned to one of the two intervention (group 1) and control (group 2) groups. The full content of the program will be visible only to the participants in the intervention group. Participants in the control group will be able to download the app after the end of the intervention to use the educational benefits of the app. A self-care application can be used online and offline designed for smartphones running the Android operating system. To run this test, eligible students are asked to install the self-care app on their smartphone and see the necessary instructions on how to work with the program in the form of a short guide on the main page of the application. Initially, the participants are asked to complete the self-care questionnaire in the form of a pre-test. Then, the educational content designed for the application is provided for individuals based on national and international guidelines and protocols of (WHO, CDC, FDA, ADF, Ministry of Health and Medicine, Health Education and Health Promotion Office). This program will be available to people for 3 months and after installing the application on their smartphone and entering the information requested from the users, educational content and reminder messages will be sent according to their conditions. In the reminders section, the user registers his health behavior based on the day, time, and number of times he wants, and a reminder is sent to him. But if the user’s self-care status after answering the self-care questions in each of the 5 dimensions of self-care is assessed as weak or average, motivational health messages are sent to the user daily in the form of notifications, so that the user is encouraged to perform self-care behaviors. The use of the application by the participants is reviewed in the management panel and health messages and incentives are provided for the use of this program. To provide support, the researcher’s phone number is given to the subjects to make a call in case of problems. Three months after the intervention, when no new content is sent to the student, the participants in both groups are requested to complete the self-care questionnaire in the form of a post-test. After the end of the data collection process, the individuals in the control group can install a mobile Application and the necessary training will be given to them after the end of the study. In the present study, content, information, and experiences reach the end users or audience with the specific purpose of self-care through mobile applications in the form of text, audio, or other art forms. Users find and use health-related self-care information through content. The graphic design of the application is based on the opinion of the research team professional designers and application development experts. The production of the content is based on the points extracted from the interviews, national and international guidelines, and protocols of (WHO, CDC, FDA, Ministry of Health and Medicine, Health Education and Health Promotion Office), for example, Australian dietary guidelines, Canberra: NHMRC [20], WHO guidelines on physical activity and sedentary behavior for children and adolescents aged 5–17 years: summary of the evidence [21], and physical activity guidelines [22].
